# 3. PROTOCOL DETAILS

## 3.1 Rationale

### 3.1.1 Long Term Follow-Up

Results of the Phase III studies have demonstrated that GARDASIL™ is highly efficacious in preventing HPV 6-, HPV 11-, HPV 16-, and HPV 18-related CIN, AIS, cervical cancer (via CIN 2/3 and AIS), VIN, VaIN, condylomata acuminata, vulvar cancer (via VIN 2/3), and vaginal cancer (via VaIN 2/3) in the group that received GARDASIL™ compared to the placebo group in subjects who were not infected by the relevant HPV type at the start of the study. The base study was conducted to bridge to GARDASIL™ studies conducted in girls and women 9-26 years of age. The long term follow-up study is being conducted to assess safety, immunogenicity, and effectiveness in the population of women vaccinated at 24 to 50 years of age through 5 to 10 years following vaccine Dose 1.

## 3.2 Study Procedures

### 3.2.1 Concomitant Medication(s)/Treatment(s)

No study vaccinations will be administered during the LTFU study. If an investigator discovers that a subject received an additional dose of GARDASIL™ outside the context of the LTFU study, such discovery should be reported to the study sponsor.

### 3.2.2 Activity and Other Prerequisites

Subjects and study personnel should adhere to the following prerequisites and if necessary, any scheduled visit may be rescheduled within the allowed time range of ± 6 months of Year 6, 8, or 10 visits.

For study visits which include pelvic exams, study personnel should verify by verbal history that:

1. Subjects have refrained from douching/vaginal cleansing or using any vaginal medication or preparation for 48 hours prior to any study visit. If the subject has not refrained from douching or using a vaginal medication or preparation during the 48 hours prior to the scheduled or unscheduled visit, the exam and specimen collection must be delayed until the 48 hour requirement is met.
2. Subjects have refrained from sexual intercourse (including anal, vaginal, or genital/genital contact whether same sex or opposite sex) for 48 hours prior to any visit (scheduled or unscheduled), in an attempt to avoid detection of viral DNA which has been deposited in the vagina or on the perineal/perianal area during sexual intercourse and is not the result of ongoing infection. If the subject has not refrained from the specified sexual activity for 48 hours prior to the scheduled or unscheduled visit, the exam and specimen collection must be delayed until the 48 hour requirement is met.
3. Subjects have had no menses within 2 days of any study visit involving specimen collection. Any visit for specimen collection should be done at least 2 days after menses is completed. If possible, no specimen should be collected within 2 days prior to menses. If, despite the above, visible blood is noted in the vagina, then the specimen may be collected. The presence of visible blood in the vagina should be noted in the data collection module.

### 3.2.3 Procedures

The Study Flow Chart summarizes procedures for scheduled study visits and items appear in the order they should be performed. This section provides clarification on the scheduled study visit procedures (presented in the same order as on the Study Flow Chart).

#### 3.2.3.1 Informed Consent

Eligible subjects will be required to re-consent prior to initiating any procedures and subjects that decline will require documentation by the site regarding the refusal.

The investigator must obtain documented consent from each potential subject in biomedical research or when an investigational vaccine is administered to subject in a clinical study. If a Patient Package Insert (PPI) exists for any product being used in the study within the indication and dosage of the prescribing information, the consent form will reference the PPI and the investigator shall provide a copy of it to the subject for his/her review before the subject signs the Informed Consent Form. If the study is outside of the indication or dosage, the consent form shall include all relevant information from the PPI but the subject will not be given a copy of the PPI.

Consent must be documented by the subject dated signature on a Consent Form along with the dated signature of the person conducting the consent discussion.

If the subject is illiterate, an impartial witness should be present during the entire informed consent reading and discussion. Afterward, the subject should sign and date the informed consent, if capable. The impartial witness should also sign and date the informed consent along with the individual who read and discussed the informed consent (i.e., study staff personnel).

If the subject is legally incompetent (i.e., a minor or mentally incapacitated), the written consent of a parent, legal guardian or legal representative must be obtained. Depending on local law or review committee requirements such consent may also need to be signed by an impartial witness.

When the study population includes non-English speaking people, the information in the consent form should be translated and communicated to the subject in language understandable to the subject. Either the investigator or Merck may take the responsibility for the translation; however, documentation must exist to demonstrate who performed the translation and that the translation was verified by an individual other than the person who performed the translation. An accurately translated consent form should be provided with a written statement by the translator (whether the translator is the investigator, the Clinical Monitor, or a professional translator), indicating that the consent form is an accurate translation of the accompanying English version.

A copy of the signed and dated consent form should be given to the subject before participation in the trial.

The initial informed consent form and any subsequent revised written informed consent form, and any written information provided to the subject must receive the IRB/IEC’s approval/favorable opinion in advance of use. The subject or his/her legally acceptable representative should be informed in a timely manner if new information becomes available that may be relevant to the subject’s willingness to continue participation in the trial. The communication of this information will be provided and documented via a revised consent form or addendum to the original consent form.

A copy of the FDA Regulations Regarding Informed Consent and the World Medical Association Declaration of Helsinki are included in the administrative binder.

#### 3.2.3.2 Randomization/Allocation

No new randomization will be performed during the LTFU study. The allocation numbers assigned to study subjects from Colombia during the base study will be carried over to the LTFU study.

A single patient/subject cannot be assigned more than 1 allocation number.

#### 3.2.3.3 Treatment/Evaluation/Follow-Up Procedures

Inclusion/exclusion criteria will be reviewed prior to enrollment or any study procedures.

All subjects/patients will be given a card, identifying them as participants in a research study. The card will contain contact information (including direct telephone numbers) to be utilized in the event of an emergency.

No vaccination will be provided in the long term follow-up study.

A plastic, non lubricated single-use, individually wrapped plastic speculum will be used for gynecologic examinations.

Please refer to the Specimen Collection Procedures Manual for step-by-step specimen collection and handling procedures.

##### 3.2.3.3.1 Summary of Scheduled Study Visit Procedures

The following visit procedures will be performed at the Year 6, Year 8, and Year 10 visits:

1. Medical history
2. Gynecologic history
3. General physical exam
   - include weight, sitting blood pressure, sitting pulse, respirations, and oral temperature
   - check the heart, lungs, thyroid, skin, and breasts
4. External portion of wart/lesion inspection (vaginal inspection will occur after all specimens are collected)
5. Pelvic Exam with plastic speculum
6. Optional tests based on clinical findings (see section 3.2.3.3.4)
7. ThinPrep™ Pap test
8. Vaginal portion of wart/lesion inspection
9. Bimanual exams or palpation of uterus and adnexa

Perform bimanual exam only after all genital samples are collected to avoid possible contamination or bleeding that might affect the quality of the samples

1. Blood collection for anti-HPV serology test
2. Safety follow-up - See Section 3.4

##### 3.2.3.3.2 Procedures During Pregnancy and Lactation

All pregnancies are to be reported to the SPONSOR. If pregnancy develops the investigator will maintain regular contact with the subject for the purpose of pregnancy assessment, including a detailed interim medical history (medical procedures and medications taken during the pregnancy). The information is to be updated at least once each trimester. Pregnancies will be followed to the completion/termination of the pregnancy. If the pregnancy continues to term, the outcome (health of infant) must be reported to the SPONSOR. Information regarding this data management procedure will be provided by the SPONSOR.

The subject will complete the study visits as per protocol and at the investigator’s discretion. Collection of samples and performance of visits and/or procedures during pregnancy are up to the local standard of care and/or the investigator’s judgment. The use of a cytobrush (Cytobrush™) for ThinPrep™ Pap test collection is contraindicated in women that are 10 weeks pregnant or more, according to the current manufacturer’s label. The use of a cyto-broom (Wallach Papette™) is not contraindicated in pregnancy, according to the current manufacturer’s label. The use of a cyto-broom instead of Cytobrush™ will be allowed if the investigator decides to perform a ThinPrep™ Pap test during pregnancy. Routine study procedures that are contraindicated during pregnancy will not be performed and the visit will be postponed until the procedures can be performed.

Information on lactation will not be collected during Protocol 019-20.

##### 3.2.3.3.3 External Genital Inspection

An external genital inspection will be conducted to ascertain the presence of genital warts/lesions in the external genital regions. This inspection will be conducted prior to the pelvic exam. Symptomatic subjects (e.g., those experiencing pruritus, discomfort, presence of lumps or bumps) may be seen at a scheduled or unscheduled visit for further evaluation.

In addition to the external genital wart/lesion inspection, a vaginal wart/lesion inspection is conducted after collection of per-protocol specimens. Please refer to the Specimen Collection Procedures Manual for step-by-step genital wart/lesion specimen collection (includes equipment list) and handling procedures.

###### 3.2.3.3.3.1 Genital Wart/Lesion Treatment and the Event of Recurrence

Management of genital warts will be at the investigator’s discretion, per the site's standards and practice. Excision of the wart is the ***preferred*** study treatment. If excision is the treatment modality chosen by the investigator, all excised tissue is to be submitted to the central laboratory for analysis.

Treatment of genital warts by topical medications and cryotherapy are acceptable study procedures; however, these treatment modalities can be performed only after completing all biopsy requirements. A biopsy of the identified lesion(s) (e.g., morphology differs among identified lesions or more than one lesion identified) must be obtained prior to administering topical medications or cryotherapy. In addition, cryotherapy is to be performed only on the external genitalia (no cervical cryotherapy is allowed). Overall, the preferred method is to biopsy and treat at the same visit.

During genital wart treatment, follow-up biopsies should be obtained if new HPV-related lesions of differing morphology, and/or differing location appear. A recurrence of a genital wart/lesion is defined as the reappearance of a lesion of similar morphology in the same anatomical location within 2 months after complete resolution of the initial lesion. Recurring lesions will not be biopsied. Otherwise, all new lesions will be biopsied.

##### 3.2.3.3.4 Optional Tests for Clinical Symptoms and Clinical Abnormalities

###### 3.2.3.3.4.1 Optional Tests for Clinical Symptoms

Optional tests may be performed, if indicated and at the investigator's discretion, at any time during the study. Procedures for collection of certain optional tests may be located in the Specimen Collection Procedures Manual. Optional tests include:

- *Neisseria gonorrhoeae* culture
- *Chlamydia trachomatis* culture
- Syphilis detection test
- Hepatitis B surface antigen (HBsAG)
- Hepatitis C surface antigen (HCsAG)
- HIV antibody test
- Swab for Herpes Simplex Virus Culture
- Vaginal pH
- Wet mount for trichomonas and bacterial vaginosis
- Whiff test for bacterial vaginosis
- KOH test for yeast

Subjects who test positive for gonorrhea, Chlamydia, syphilis, HIV, hepatitis B, or hepatitis C should be referred for appropriate counseling and treatment. Treatment for Chlamydia or gonorrhea can be administered following specimen collection.

###### 3.2.3.3.4.2 Clinical Abnormalities

Any clinical abnormalities found at any time during the study will be referred for appropriate care:

- Vaginitis may be managed by the investigator according to the local standard of care only after visit procedures are performed.
- Cervicitis may be managed by the investigator. If there is clinical evidence of gross purulent cervicitis during a scheduled visit that involves a pelvic exam, the specimen collection should be postponed until after treatment or determination of nonspecific identifiable etiology.

##### 3.2.3.3.5 Pap Test for Liquid Cytology (ThinPrep™)

A ThinPrep™ Pap test for cytology will be performed at Year 6, Year 8, and Year 10 visits. All ThinPrep™ Pap tests will be tested at a cytology laboratory selected by the SPONSOR. Cytology specimens will be evaluated using the Bethesda System—2001. For all cytology diagnoses of Atypical Squamous Cells of Undetermined Significance (ASC-US), the SPONSOR central laboratory will automatically perform reflex HPV testing on residual ThinPrep™ material, using the Digene Hybrid Capture II™, High Risk/Low Risk Probes. If at least 1 probe is positiveor if no result is obtained, the subject will be referred for colposcopy. If both probes are negative, the subject will return for Pap screening at the routine visit interval. Colposcopy is recommended for the cytology diagnosis of Atypical Squamous Cells, and cannot rule out high grade squamous epithelial lesions (ASC-H). All Pap reports should be reviewed and signed by an M.D. or D.O. investigator/subinvestigator.

Procedures should be performed for all subjects as per the protocol mandated instructions located in the SPONSOR’s Specimen Collection Procedures Manual. Specimens must also be shipped according to instructions summarized in the SPONSOR’s Specimen Collection Procedures Manual.

##### 3.2.3.3.6 Serum for Antibody Measurements

Cohort 1, the subjects vaccinated with GARDASIL™ on Day 1, will undergo anti-HPV serology testing at approximately 6, 8 and 10 years following Day 1 for anti-HPV 6, 11, 16, and 18 responses (see Section 3.3.3 for description of the cLIA assay used). Cohort 2, the subjects who were allocated to receive placebo during the base study, will be enrolled in the long term follow-up extension following receipt of GARDASIL™ in the first extension (Protocol 019-10). This cohort will have similar calendar time points for serological testing which correspond to approximately 1, 3, and 5 years following vaccination with GARDASIL™.

Please refer to the Specimen Collection Procedures Manual for step-by-step procedures for blood (serum) and retention serum collection and handling guidelines.

##### 3.2.3.3.7 Colposcopy/Biopsy/ Definitive Therapy Procedures

###### 3.2.3.3.7.1 Triage for Abnormal Pap Tests

Subjects with ThinPrep™ Pap tests obtained during the study showing abnormalities should be referred to colposcopy and biopsy according to the Mandatory Algorithm for Triage of Abnormal Pap tests to Colposcopy provided in Table 3-2. This is a protocol-prescribed strategy and any deviation will require prior approval by the SPONSOR. Colposcopy may also be performed in the case of an unresolved post-coital bleeding that persists after completion of appropriate work-up. Prior to a colposcopy for this indication, the case must be reviewed with the SPONSOR and a note to file must be generated.

If a subject is scheduled to undergo a hysterectomy, a colposcopy with biopsy should be performed.

Table 3-2

Mandatory Algorithm for Triage of Abnormal Pap Tests to Colposcopy

| ThinPrep™ Pap Result | Action |
| --- | --- |
| Negative for intraepithelial lesion or malignancy (includes reactive, reparative, inflammatory, etc.) | Routine visit interval as specified by the protocol. |
| Atypical Squamous Cells—Undetermined Significance (ASC-US) | Central laboratory performs reflex HPV testing on residual ThinPrep™ material (High Risk and Low Risk Probe, Hybrid Capture II, DIGENE™). If at least 1 probe is positive or if no result is obtained, the subject will be referred for colposcopy. If both probes are negative, then the subject will return for Pap screening at the routine visit interval. |
| Atypical Squamous Cells—cannot exclude HSIL (ASC-H) | Referral to colposcopy. |
| Low-grade Squamous Intraepithelial Lesion (LSIL) | Follow-up in 6 months |
| High-grade Squamous Intraepithelial Lesion (HSIL) | Referral to colposcopy. |
| Atypical Glandular Cells (to include atypical endocervical, endometrial, NOS; Adenocarcinoma in Situ, adenocarcinoma, etc.) | Referral to colposcopy. |
| Unsatisfactory | Repeat ThinPrep™ Pap test as soon as possible, but not less than 4 weeks from the Pap test that had the unsatisfactory finding. |
| Colposcopy should be performed according to the guidelines in this table or as indicated clinically over the ensuing period of follow-up.  Colposcopy must be performed within 2 months of the abnormal Pap result that required the referral to colposcopy. | |

###### 3.2.3.3.7.2 Colposcopy

All colposcopies will be performed at the study site. Colposcopy will be performed only by an experienced colposcopist (>50 colposcopies per year for at least 2 years). Subjects who undergo colposcopy may undergo biopsy if clinically indicated. Each discrete abnormal area that is observed on colposcopy should be biopsied. Separate biopsy forceps must be used for each of the discrete lesions that are biopsied.

To ensure that colposcopy practices and skill levels are standardized across investigator sites and colposcopists at all sites develop a uniform approach to all study colposcopies, colposcopists will be required to participate in Colposcopic Standardization Training. The purpose of this training is to evaluate the colposcopic practices at all investigator sites, to standardize colposcopy and biopsy practices, and to provide a guide for all aspects of the protocol related to colposcopy and histologic sampling of the cervix. An alternative to the SPONSOR organized colposcopy training, the “Comprehensive Colposcopy Course,” given by the American Society for Colposcopy and Cervical Pathology (ASCCP) will be accepted as equivalent for the purpose of standardization to participate in this study, provided it has been taken within a year of study startup.

If no lesion is noted on colposcopy, and the subject was referred based on a cytologic abnormality, endocervical curettage (ECC) may be performed if it is deemed by the investigator to be medically indicated. A curet may be used, but not a cytobrush, when obtaining the ECC specimen.

Please refer to Specimen Collection Procedures Manual for guidelines for colposcopic procedures.

###### 3.2.3.3.7.3 Procedures for Biopsy and Definitive Therapy

The following are general procedures for external genital biopsy, cervical biopsy, and definitive therapy that may be performed during the study. Specific step-by-step procedures can be found in the Specimen Collection Procedures Manual provided by the SPONSOR.

***Genital Wart/Lesion Biopsy***

Genital wart biopsy may be conducted at a scheduled or unscheduled visit. If a suspected lesion(s) (possibly, probably, or definitely HPV-related per the investigators judgment, or of unknown etiology) is identified in the vagina, vulvar, periurethral, perineal, and/or perianal region, a biopsy specimen is to be obtained and submitted to the central laboratory designated by the SPONSOR for review by a pathologist for the purpose of management of the subject. It is important to make an accurate evaluation of any identified lesions observed during the study on all study participants. After a thorough examination:

- The investigator should provide a clinical impression of the lesion, which should include 1 of the following: condyloma acuminata, a flat wart, a papular wart, a keratotic wart, other HPV-related lesion (e.g., VIN, Bowenoid papulosis, Bowen’s disease), or other non-HPV-related lesion.
- The location and anatomical area of each biopsied wart/lesion should be identified and noted (as per lab kit requisition supplied by the SPONSOR) and should also be recorded according to data management guidelines.
- Any suspicious area identified should be biopsied for evaluation.
- For multiple warts, select 1 external wart to biopsy that is most representative of the morphology and is most accessible.
- Additional biopsies may be performed either for warts in a different anatomical area and/or for warts that have a different clinical impression. For each biopsy, different instruments are to be used to prevent cross-contamination between specimens.
- Identified vaginal lesions (VaIN) are to be collected in a separate vaginal biopsy kit. Treatment for VaIN is per investigational site’s standards and practices.

Please refer to the Specimen Collection Procedures Manual for step-by-step genital wart/lesion biopsy collection and handling procedures.

Slides of wart/lesion biopsy or vaginal biopsy specimens will be prepared at the central pathology laboratory and reviewed by a pathologist for the purpose of management of the subject. The slides prepared from the genital wart/lesion biopsy (external and vaginal), as well as the investigator’s observation of whether the lesion is single or there are multiple lesions, will be submitted to the Independent Pathology Panel which will provide the final diagnosis for study purposes. The slides will be returned to the originating central pathology laboratory at the completion of review by the panel.

If the diagnosis of the Independent Pathology Panel is VIN 3/VaIN 3 or worse, and the diagnosis of the central laboratory is of lower grade abnormality, then the investigator will be notified of the discrepant diagnoses. The Independent Pathology Panel will be blinded to the results of the PCR analysis of the biopsy.

External genital and vaginal biopsy specimens will be sent to the SPONSOR's designee for HPV analysis. HPV analysiswill be performed on Thinsection microtomy specimens. Each biopsy specimen will be analyzed by HPV PCR, regardless of whether an HPV-related histologic diagnosis is made, for the purpose of determining the causal HPV type in the lesion. HPV typing will be performed using Multiplex PCR Assay to detect vaccine HPV types. Samples that test negative for HPV vaccine types will be analyzed for non-vaccine HPV types using type-specific PCR for multiple high-risk HPV types. The interval between the genital wart/lesion biopsy and the next scheduled study visit that includes a complete gynecological examination must be ≥2 months.

Treatment for VIN, VaIN, and genital warts is per the investigational site’s standards and practices. During genital wart treatment, follow-up biopsies should be obtained if new HPV-related lesions of differing morphology, and/or differing location appear. A recurrence of a lesion is defined as the reappearance within 2 months of a lesion of similar morphology in the same anatomical location after complete resolution of the initial lesion. Recurring lesions will not be biopsied. Otherwise, all new lesions will be biopsied.

**A subject with an external genital lesion that is histologically confirmed to be HPV-related (e.g., VIN, VaIN, and genital warts) by the SPONSOR central laboratory is to be referred to colposcopy.**

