## 1.4 Summary of Study Design

This Long Term Follow-up (LTFU) is a safety, immunogenicity, and effectiveness observational study. All subjects will sign an informed consent prior to initiation of any study procedure. Subjects will have been enrolled in the Protocol 019 base study in Colombia. Approximately 1,600 healthy women who meet the eligibility criteria will be invited to participate. The age of the women at the time of vaccination Dose 1 will range from 24 to 45 years of age among GARDASIL™ recipients in the base study and 29 to 50 years of age among placebo recipients in the base study.

HPV-related analyses will include: HPV type-specific PCR-based assays to determine the causal HPV type within a clinical lesion (such as a genital wart or a CIN2+ lesion).

The study will have general guidelines for referral of subjects for colposcopy and biopsy during the follow-up period. All biopsy specimens will also undergo HPV DNA analysis using Thinsection PCR. All biopsies will be analyzed at the central laboratory designated by the SPONSOR. The diagnoses provided by the lab will be used for routine management of subjects. However, the diagnoses provided by the lab will not represent the official diagnoses for study purposes. The slides will subsequently be reviewed by an Independent Pathology Panel; the consensus diagnosis of the Independent Pathology Panel will represent the final diagnosis for study purposes.

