***Cervical Biopsy and Endocervical Curettage***

If cervical biopsies and/or endocervical curettage (ECC) specimens are obtained, specimens must be sent to the central laboratory designated by the SPONSOR for analysis. This unscheduled visit(s) will be considered part of the study and any specimens collected will be handled in a protocol-specified manner.

Slides of cervical biopsy/ECC specimens will be prepared at the central laboratory selected by the SPONSOR and reviewed by a pathologist for the purpose of management of the subject. The slides will subsequently be reviewed by the Independent Pathology Panel for consensus diagnosis. The slides will be returned to the originating central pathology laboratory at the completion of review by the panel.

The investigator will be notified of any histologic diagnosis made by the Independent Pathology Panel that is more severe than the one made by the central laboratory pathologist. For the purposes of this protocol, the SPONSOR and the central laboratory have defined a discordant diagnosis as a case in which the Thin Prep™ Pap test is more severe than the subsequent cervical biopsy (and ECC, if obtained) diagnosis and the Pap test diagnosis would ultimately lead to definitive therapy. If the Pap diagnosis is AGC, AIS, ASC-H or LSIL, cannot exclude HSIL and the biopsy diagnosis is CIN 1 or less, then this is defined as discordant. The investigator will be notified of all discordant diagnoses. A discordant diagnosis will require a review of the results. If upon review the results are amended, the triage algorithm should be followed (if the Pap results are amended, i.e., not HSIL, not AGC, not ASC-H, then follow the routine visit schedule, or if the biopsy results are amended to show CIN 2/3 or worse, proceed to definitive therapy). If the discordant results are reviewed but not amended, a repeat Pap and a colposcopy/ECC are required (≥2 months after the last colposcopy/ECC). If the diagnosis of the pathology panel is CIN 2/3 or worse, and the diagnosis of the central laboratory is of a lower grade abnormality, then this is defined as a safety net case. Safety net notification does not require a review of the results.

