***Referral for Definitive Therapy***

Subjects who undergo cervical biopsy during the study will be referred for definitive therapy according to mandatory protocol prescribed guidelines including:

- Biopsy-confirmed CIN 2, CIN 3, or cervical cancer
- Two repeat HSIL diagnoses (regardless of whether they are consecutive or not) on ThinPrep™ Pap test without confirmed CIN 2, CIN 3, or cervical cancer on biopsy or ECC
- An ECC demonstrating CIN 2, CIN 3, AIS, or cervical cancer
- A single HSIL Pap with an unsatisfactory colposcopic examination including a negative examination of the vagina and a negative ECC
- Atypical Glandular Cells or AIS on Pap result with unsatisfactory colposcopy or negative biopsy or ECC; or

Flow charts illustrating these indications for definitive therapy is provided in Section 7 (Attachments).

Cervical tissue specimens will be submitted to the central laboratory selected by the SPONSOR for histopathologic review. In addition, specimens will be prepared by the central lab for HPV PCR analysis by the SPONSOR or its designee using the Multiplex PCR Assay to detect vaccine and non-vaccine HPV types on all samples.

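### For external genital and vaginal specimens, notice to the investigator of a worse Panel diagnosis is required only from VIN 3/VaIN 3, while for cervical specimens any worse Panel reading must be reported

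*Protocol*

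**What the plan says.** Section 1.4 separates two uses of histology. Of the central laboratory it says "The diagnoses provided by the lab will be used for routine management of subjects", and it makes the Panel's consensus the final diagnosis for study purposes. The Genital Wart/Lesion Biopsy text in Section 3.2.3.3.7.3 repeats the split: suspected lesions go to the central laboratory "for review by a pathologist for the purpose of management of the subject", and the slides then go to the Panel.

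That section has one notification rule for external genital and vaginal specimens. It opens "If the diagnosis of the Independent Pathology Panel is VIN 3/VaIN 3 or worse", adds the condition that the laboratory graded the lesion lower, and then requires the investigator to be told. Its colposcopy referral depends on the laboratory alone: a subject is covered if her external genital lesion is "histologically confirmed to be HPV-related (e.g., VIN, VaIN, and genital warts) by the SPONSOR central laboratory is to be referred to colposcopy".

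The next part, Cervical Biopsy and Endocervical Curettage, has a wider rule. There the requirement is that the site is "notified of any histologic diagnosis made by the Independent Pathology Panel that is more severe than the one made by the central laboratory pathologist". A separate safety-net definition follows, beginning "If the diagnosis of the pathology panel is CIN 2/3 or worse".

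Sections 1.3 and 3.1.1 describe prevention of vulvar and vaginal cancer as working through VIN 2/3 and VaIN 2/3.

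**The concern.** When care follows one reading and study classification follows another, a rule is needed to carry a worse second reading back to the person giving care. The protocol has such a rule for both specimen types but sets it differently. For vulvar and vaginal tissue it starts at grade 3, although the protocol's own rationale groups grade 2 with grade 3 as a cancer precursor.

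What is at stake is information for care. A woman could have a Panel VIN 2, or a Panel wart that counts as an effectiveness case under Section 2.5.2 if a vaccine type is found, while nothing in the available text requires her investigator to learn of that diagnosis. If the laboratory had called the lesion not HPV-related, the histology-based colposcopy referral would not be triggered either.

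**Working it through.** No arithmetic applies. The check is to read the rules together and ask what each combination of readings requires.

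**Scope of the wider rule.** It could be argued that the cervical sentence, which speaks of any histologic diagnosis, covers all specimens. It stands under a cervical/ECC sub-heading and directly follows text on cervical and ECC slides. Reading it across would also leave the VIN 3/VaIN 3 condition with nothing to do. It is therefore confined to cervical specimens.

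**Required actions for external genital and vaginal specimens.**

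| Panel reading | Laboratory reading | Notice required? | Histology-based colposcopy referral? |
| --- | --- | --- | --- |
| VIN 3/VaIN 3 or worse | lower grade, still HPV-related | yes | yes |
| VIN 2/VaIN 2 | VIN 1, VaIN 1 or wart | no | yes, on the laboratory reading |
| Wart, VIN 1–2 or VaIN 1–2 | not HPV-related | no | no |

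Under the cervical rule, all three rows would be notified. With a floor at VIN 2/VaIN 2, the second row would be notified, but the third only where the Panel read grade 2.

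**Other routes to the investigator.** The Year 6 and Year 8 reports described in Section 3.3.2 give sites aggregate, cohort-level PCR results. They are not described as giving histology on individual women.

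**Effect on endpoints.** Cases are classified on the Panel diagnosis (Sections 2.5.2 and 2.7), and VIN and VaIN are not among the Section 2.5.2 effectiveness endpoints. The notification floor does not change how any specimen is classified.

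**The case against.** The strongest reply is that the two floors follow from the actions attached to them. "Biopsy-confirmed CIN 2, CIN 3, or cervical cancer" is a mandatory indication for definitive therapy, so a missed CIN 2 breaks a protocol rule. For the lower genital tract the protocol says "Treatment for VIN, VaIN, and genital warts is per the investigational" site's own practice, and no visible protocol action depends on grade 2. This explains why the cervical safety net starts at CIN 2/3. It does not explain the general cervical rule, which also covers upgrades too minor to trigger definitive therapy. And where care is left to the site, the clinician deciding on it has the more reason to know the higher reading.

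A second reply is that existing safeguards already cover most of the risk. Every woman has external and vaginal inspection and a Pap test at Years 6, 8 and 10, with mandatory triage of abnormal results. New lesions are biopsied, and biopsy with treatment at the same visit is preferred. Symptomatic women may be seen between visits, and Table 3-2 allows colposcopy when clinically indicated. The investigator also saw the lesion and thought it worth a biopsy. All of this stands and keeps the point at low priority. It does not secure that the Panel reading reaches the investigator.

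A third reply is that the Panel's established review guidelines (Section 3.3.7.2) and the attached Investigator Aids (Section 7) are not shown and may contain a rule. That also stands, so the point is limited to the text available.

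A reader might infer more: that the protocol forbids notice below grade 3, that affected women go without care, or that effectiveness estimates are biased. The documents do not support these readings. The text does not require notice below the floor but nowhere prohibits it, the safeguards above remain, and endpoint classification is untouched.

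**Conclusion.** The point holds as a low-priority, inexpensive patient-safety improvement. The protocol states a clear rule whose floor is poorly placed against its own cervical rule and its own description of grade 2 lesions as precursors. The more important gap is the Panel HPV-related lesion below grade 3 that the laboratory read as not HPV-related, because there neither notice nor referral is required. Where the laboratory read VIN 1, VaIN 1 or wart, referral already applies and less is lost.

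No size can be given. A reader might be tempted to build a count from the external genital lesion incidences in Table 3-6, but those are HPV 6/11-related cases, not VIN or VaIN rates, and no laboratory–Panel disagreement rate is given to apply to them. The number of women affected is unknown.

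The conclusion assumes that the Panel guidelines and Investigator Aids do not already require wider notice.

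**What to change.** Replace the threshold sentence in Genital Wart/Lesion Biopsy with the cervical rule: *the investigator is to be told whenever the Panel's histology on an external genital or vaginal specimen is worse than the laboratory's, including when the Panel finds an HPV-related lesion and the laboratory did not.* The minimum alternative is to lower the floor to VIN 2/VaIN 2. That covers grade 2 but leaves a Panel wart, VIN 1 or VaIN 1 unreported when the laboratory read the lesion as not HPV-related.

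Colposcopy after notice stays at the investigator's discretion, as Table 3-2 already permits, so the change secures notice and not referral. The notice carries histology only, so site blinding to subject-level PCR results under Section 3.3.2 is kept.

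The cost is one sentence in an amendment and some letters, from readings the Panel already makes. Some letters will change no care. A few may prompt extra discretionary colposcopies, which could slightly alter cervical case-finding. That should be noted when follow-up cervical incidence is set against the base study in the Table 3-4 comparisons.
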